## Abstract

**Background:**

Psychotic disorders are a serious mental health problem. Intervention before the onset of psychosis might result in delaying the onset, reducing the impact or even preventing the first episode of psychosis. This study explores the effectiveness of cognitive behavioural therapy (CBT) in targeting cognitive biases that are involved in the formation of delusions in persons with an ultra-high risk for developing psychosis. A single blind randomised controlled trial compares CBT with treatment as usual in preventing or delaying the onset of psychosis.

**Method/design:**

All help seeking patients aged 14 to 35 years referred to the mental health services in three regions in the Netherlands are pre-screened with the Prodromal Questionnaire during a period of two years. Patients with a score of 18 or more on the sub-clinical positive symptoms items (45 items in total) will be assessed with the Comprehensive Assessment of At Risk Mental State (CAARMS). In a different pathway to care model all referrals from the mental health services in Amsterdam to the specialized psychosis clinic of the Academic Medical Centre in Amsterdam are also assessed with the CAARMS. The primary outcome is the transition rate to psychosis according to the CAARMS-criteria. Group differences will be analysed with chi-square tests and survival analyses.

**Discussion:**

CBT is a highly tolerated treatment. The psycho-educational CBT approach may prove to be a successful strategy since most people with an At Risk Mental State (ARMS) are distressed by odd disturbing experiences. Giving explanations for and normalising these experiences may reduce the arousal (distress) and therefore may prevent people from developing a catastrophic delusional explanation for their odd experiences and thus prevent them from developing psychosis.

Screening the entire help-seeking population referred to community mental health services with a two-stage strategy, as compared with traditional referral to a specialist clinical psychosis centre, might detect more ultra-high-risk (UHR) patients. This type of screening could be implemented in mental health care as routine screening. The trial is registered at Current Controlled trials as trial number ISRCTN21353122.

## Background

In recent decades, the number of studies on early detection and intervention in psychosis has increased exponentially. In the UK [1,2], Australia [3], Norway [4] and the Netherlands [5], specialized programs have been developed for first psychotic episode patients. An unexpected finding in a seminal study was the identification of a group of help-seeking young people with sub threshold psychotic symptoms that made a transition to psychosis [6]. This phase prior to a first episode of psychosis, retrospectively called the prodromal period, begins with the first changes in behaviour and lasts until the onset of the first psychotic episode [7]. The prodromal period can be characterized by various mental state features, including non-specific symptoms such as depressed mood and anxiety, negative signs and symptoms as well as sub-threshold or attenuated psychotic symptoms [6]. However, the term "prodromal" is not always correct in prospective investigations. After all, only in the at risk people who actually develop a full-blown psychosis, the symptoms can be defined as 'prodromal'. The majority of individuals who share the same sub-clinical symptoms will recover spontaneously or have persistent sub-clinical symptoms [8] without a transition into psychosis. Instead of putatively prodromal, in prospective studies the subjects are referred to as being at ultra high risk (UHR) or having an At Risk Mental State (ARMS) of developing psychosis.

Yung and McGorry were the first to develop operational criteria to detect people at ultra high risk of developing psychosis, resulting in the Comprehensive Assessment of At Risk Mental State (CAARMS) scale [8]. At first about 40% of the people with ARMS made a transition to psychosis within a year [8,9]. However, more recent studies find lower transition rates (declining to only 16% transition to psychosis at 24 months) [10,11].

The identification of people at high risk for developing psychosis has been replicated in several studies in Australia, Europe and the USA [12-15]. People with an ARMS experience (mild) symptoms, are often help-seeking and frequently suffer psychosocial impairment and disability [6]. Therefore one important aspect of the ARMS is that it is a status in which an intervention could be delivered to prevent transition. Detection of people with ARMS is therefore required. When people do make a transition then the potential duration of untreated psychosis is probably short. Previous research has shown that a shorter delay in treating the first episode of psychosis is associated with a better outcome [16]. Intervening before the first psychotic episode can thus be a valuable treatment option. The aim is reduction of high risk symptoms and to try to prevent or delay the onset of psychosis as well as a reduction of suffering from psychological impairments [13].

Several intervention studies have been performed in the ARMS-group [3,12,14,15,17]. Interventions in these studies include prescribing drugs (anti-psychotics or others), cognitive behavioural therapy (CBT) or a combination of these treatments. One study delivers a complete treatment package to the patients [15]. These studies suggest that an intervention may reduce the transition to psychosis in the short term. Recently published reviews on interventions in people at high risk for developing psychosis concluded that the effects of interventions are currently indecisive, implying that more research is necessary [18,19].

### Aim

The objective of this study is to test a manualised CBT aimed at reducing the transition rate to psychosis and to reduce the number of patients with persistent ARMS-symptoms. This CBT is largely based on the work of French and Morrison [14,20,21] who developed a promising intervention for reducing or postponing the transition to psychosis in the short term. The intervention is enriched with information on cognitive biases and exercises to learn to correct these biases.

## Methods/Design

### Design

This study is a randomized controlled trial comparing treatment as usual (TAU) with an add-on cognitive behavioural therapy (CBT) targeted at the prevention of psychosis. The main outcome measure is the number of participants who develop florid psychosis within eighteen months. The secondary outcome is the reduction of the persistence of sub clinical symptoms.

The assessors are blinded to the research condition by not being able to check the patient status. The success of blinding is checked by having the assessors guess the presumed condition of the subject at each major assessment.

The design of this study has been approved by the Dutch Union of Medical-Ethics Trial Committees for mental health organizations. The trial will be conducted in compliance with the 'Declaration of Helsinki' (amendment of Edinburgh, 2000).

### Participants

All patients aged 14 to 35 years referred to the mental health services in The Hague, Rivierduinen (Leiden and surroundings) and the province of Friesland in the Netherlands will be pre-screened with the Prodromal Questionnaire [22] over a period of two years. Patients with a score above the cut-off point of 18 on the positive symptom subscale (45 items in total) will be assessed with the CAARMS [8]. Furthermore, all patients with a suspicion of a psychotic development referred by the mental health services in Amsterdam to the specialized early psychosis clinic of the department of Psychiatry at the Academic Medical Centre will be assessed with the CAARMS. Participants are eligible if the following criteria are met: a) age 14 to 35 years; b) a genetic risk or CAARMS-scores in the range of At Risk Mental State (See table 1, 2, 3); and c) an impairment in social functioning, (a SOFAS- score [23] of 50 or less and/or a drop in SOFAS score of 30%.). Patients are excluded if they meet any of the following criteria: a) current or previous usage of antipsychotic medication more than 15 mg Haloperidol equivalent; b) severe learning impairment; c) problems due to organic condition; d) insufficient competence in the Dutch language; e) history of psychosis.

**Table 1 T1:** group 2a Attenuated psychotic symptoms, Sub-threshold intensity

	Intensity	Frequency
Unusual Thought Content	3-5	3-6

Non-bizarre Ideas	3-5	3-6

Perceptual Abnormalities	3-4	3-6

Disorganised Speech	4-5	3-6

**Table 2 T2:** group 2b Attenuated psychotic symptoms, sub-threshold frequency

	Intensity	Frequency
Unusual Thought Content	6	3

Non-bizarre Ideas	6	3

Perceptual Abnormalities	5-6	3

Disorganised Speech	6	3

**Table 3 T3:** group 3, BLIPS Group

	Intensity	Frequency
Unusual Thought Content	6	4-6

Non-bizarre Ideas	6	4-6

Perceptual Abnormalities	5-6	4-6

Disorganised Speech	6	4-6

Symptoms occur less than one week and resolve spontaneously

Participation is voluntary. Informed consent is given in writing and with personal signatures. Persons under 16 years also require informed consent from a parent. Participants may withdraw their informed consent at any time, without any consequences for their treatment.

### Randomisation

Randomisation will be stratified by site, to rule out factors concerning the institutions, therapists and habitat. The random allocation lists are generated by a web-based automated randomization system. To guarantee a numeric balance across conditions the randomisation will be performed separately for each research site, in random permuted blocks of ten. The allocation list will be kept in a remote secure location and an independent person randomly allocates the included patients. Patients are randomised after providing informed consent. The randomisation status is confirmed by fax to the randomisation bureau by the different sites.

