### Power calculation

We calculated power on an expected transition rate of 35 percent over eighteen months with a 50 percent reduction of transitions in the CBT-group. The sample we need for a 2-tailed test of the proportions with an alpha of .05 and a power of .80 is 2 × 93 for the reduction of the transition to psychosis and 2 × 82 for the persistence of ARMS and 2 × 91 for the transition into psychosis. A conservative estimate of the drop-out rate is twenty percent per year in schizophrenia research [24]. With an estimated 30 percent drop-out over 18 months, we decided to include 240 persons in the trial. Interventions to minimize drop-outs are flexibility to location of therapy (the appointment can be at their home-address or some times by telephone or webcam), sending Christmas- and Birthday cards every year. For the participants that end up in the CBT-treatment group there is also the possibility for web-cam therapy. All the participants that complete the study will have a financial compensation for expenses made.

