### Intervention

Participants in the control condition will receive treatment as usual (TAU) for the mental problems that they are seeking help for (e.g., depression, ADHD or anxiety disorder). The subjects in the intervention group will receive TAU plus a manualised cognitive behavioural therapy (CBT). The intervention protocol, based on the protocol from the British intervention trial [20,21], is a cognitive behavioural intervention that aims to reduce symptoms, normalises psychosis-like experiences and prevents a catastrophic appraisal of the psychotic-like symptoms from occurring. The idea is that the final common pathway from ARMS to psychosis is largely based on catastrophising the psychotic-like symptoms which are then worsened by a high level of emotional arousal. When the appraisals become fixed and frightening, delusions are formed. The therapy manual in this study is enriched with eight sessions of psycho-education and behavioural experiments with cognitive biases that play a role in the development of delusions and hallucinations. Normalising the odd experiences as a result of perceptual and reasoning biases is supposed to reduce the emotional arousal and over-involvement with the experiences. Catastrophic delusional interpretation of the unsettling experiences is then probably prevented. Behavioural experiments and homework exercises teach people to tolerate psychosis-like experiences and reduce emotional discomfort. The intervention consists of a maximum of 25 sessions within a six-month period. All therapists are psychologists or consultant psychiatrists experienced in CBT with psychotic patients. They are trained in using the protocol and are offered supervision every two weeks during the course of the trial. During the two-hour supervised sessions, audio-taped sessions are discussed and rated on the Cognitive Therapist Scale [25]. Another part of the supervised sessions is dedicated to case formulation and trouble shooting of difficult cases.

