### Fidelity checks

The inter-rater reliability of the CAARMS assessments will be fine-tuned every three months in a Group wise assessment and discussion of role-played cases. The reliability of each rater is assessed by monthly independent ratings of written reports of a CAARMS interview.

The inter-rater reliability of the assessment of the fidelity of therapists in delivering the manualised therapy is fine-tuned monthly in a Group wise assessment of audio taped sessions. The fidelity of each individual therapist is assessed by a sample of five audio-taped therapy sessions rated independently by five different assessors.

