### Analyses

To determine baseline balance, several variables that are proven to be risk factors will be assessed, such as severity of ARMS-symptoms [43], heredity [44], growing up in a big city, stress and unhealthy behaviour of mother during pregnancy [45], migration and feelings of discrimination [35,36] and alcohol and drug use, including cannabis use [46]. If the baseline balance is disturbed, the analyses will be corrected for risk factors for transition to psychosis.

Missing data will be imputed by EM-algorithm. EM-algorithm recovers the complete factor loadings considerably better than simple imputation techniques [47,48].

Group differences will be analysed by unadjusted chi-square. Pearson's chi-square tests will be performed to analyse gender differences between the transition group and the non-transition group, Comparisons will be analysed on intention-to-treat, using the Statistical Package for the Social Sciences (SPSS for windows, version 17). Multiple logistic regression analyses will be used to explore which factors predict transition to psychosis within the UHR-group. To examine the effects of CBT on the positive symptoms reported on the first four scales of the CAARMS, analysis of co-variance will be used.

Survival analyses will be used to measure time to transition and risk factors for developing a first episode psychosis. We will conduct Kaplan-Meier curves to explore the cumulative probability of developing psychosis with inclusion in the study as entry point and last follow-up assessment after 18 months as the end point.

We will use the Mann-Whitney test to examine if people who made a transition scored significantly higher on the CAARMS and the SOFAS compared to patients who did not make a transition. We considered p-values less than 0.05 to be statistically significant.

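### Stratifying by site cannot rule out CBT-therapist effects, and the unadjusted chi-square leaves any clustering by therapist out of its standard error

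*Protocol article*

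**What the plan says.** All references are to the protocol article, under Methods/Design.

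- **Randomisation** gives the reason for the stratum: "Randomisation will be stratified by site, to rule out factors concerning the institutions, therapists and habitat". It adds: "To guarantee a numeric balance across conditions the randomisation will be performed separately for each research site, in random permuted blocks of ten". Therapist is not a stratification factor.
- **Intervention** describes the control arm: "Participants in the control condition will receive treatment as usual (TAU) for the mental problems that they are seeking help for". The manualised CBT, with its own trained and supervised therapists, is added in the intervention arm only.
- **Fidelity checks** shows that there are several such therapists: "The fidelity of each individual therapist is assessed by a sample of five audio-taped therapy sessions rated independently by five different assessors". Their number and caseloads are not given.
- **Analyses** fixes the comparison: "Group differences will be analysed by unadjusted chi-square". The one adjustment foreseen concerns baseline factors: "If the baseline balance is disturbed, the analyses will be corrected for risk factors for transition to psychosis". Survival analyses are also planned. No therapist or site term is named for any of these.
- **Power calculation** sizes the trial on independent patients, with no design effect for therapist.

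**The concern.** Randomising within site makes the two arms alike in whatever differs between sites before allocation. A CBT therapist is met after allocation and has no counterpart in the control arm, so there is nothing on the other side to balance against. This is a partially nested design: CBT patients are grouped by therapist, and control patients are not grouped by any CBT therapist.

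If some therapists achieve better results than others, two patients of the same therapist are more alike than two patients of different therapists. The transition rate in the CBT arm then varies more than binomial sampling allows. A chi-square on the pooled counts omits that extra variance, so its p-value can be too small and the matching confidence interval too narrow. The rationale as worded also invites the reader to think that the therapist question has been settled by design.

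At stake are the error rate of the main comparison and the width of its interval. Bias from allocation is not at issue.

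**Working it through.** **1. Inputs from the article.** Control rate: "We calculated power on an expected transition rate of 35 percent over eighteen months". A halving gives 17.5% with CBT. Test two-sided at 0.05, power 0.80, stated need 93 per arm, 240 randomised, so 120 per arm.

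**2. The plan's own figure, without clustering.** With p1 = 0.35, p2 = 0.175 and mean 0.2625, the sum of p(1−p) over the arms is 0.2275 + 0.144375 = 0.371875, and 2 × 0.2625 × 0.7375 = 0.387188.

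- Unpooled: (1.96 + 0.8416)² × 0.371875 / 0.175² = 95.3, so 96 per arm.
- Pooled: (1.96 × √0.387188 + 0.8416 × √0.371875)² / 0.175² gives 99 per arm.

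The stated 93 comes close but is not reproduced exactly; power at 93 per arm is 0.78 by the pooled formula. None of these figures includes a therapist effect.

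**3. Variance with one clustered arm.** Let m be the analysed patients per CBT therapist. The CBT-arm variance is multiplied by DE = 1 + (m − 1) × ICC; the control-arm variance is unchanged. With equal rates and equal arms:

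- true SE / chi-square SE = √((1 + DE)/2)
- true type I error = 2 × (1 − Φ(1.96 / that ratio))

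Example, m = 10 and ICC = 0.05: DE = 1 + 9 × 0.05 = 1.45; ratio = √1.225 = 1.107; 1.96/1.107 = 1.771; type I error 7.7%.

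**4. Range.** Caseload and ICC are assumptions; the article gives neither. With 120 CBT patients, caseloads of 5 to 15 correspond to 24 down to 8 therapists.

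| ICC | m = 5 | m = 10 | m = 15 |
|---|---|---|---|
| 0 | 5.0% | 5.0% | 5.0% |
| 0.01 | 5.2% | 5.5% | 5.8% |
| 0.02 | 5.5% | 6.1% | 6.6% |
| 0.05 | 6.2% | 7.7% | 9.2% |
| 0.10 | 7.4% | 10.4% | 13.3% |

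Two separate simulations (beta-binomial therapist effects in the CBT arm, 120 per arm, 35% in both arms) agree to within a few tenths of a point: at m = 15 they gave 6.4% and 6.7% for ICC 0.02, and 9.5% and 9.3% for ICC 0.05.

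**5. Interval and power at the planned effect (m = 10, ICC = 0.05).** SE ratio = √((0.2275 + 0.144375 × 1.45)/0.371875) = 1.084, so a nominal 95% interval covers about 93%. With the correct variance, power at 93 per arm is 0.70 instead of 0.78, and 80% power needs 119 per arm instead of 99.

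**6. What the ICC values mean.** At a rate of 0.35, the between-therapist SD of the true transition rate is √(ICC × 0.35 × 0.65): about 7 percentage points at ICC 0.02, 11 at 0.05 and 15 at 0.10. The whole planned effect is 17.5 points.

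**The case against.** **The sentence may mean other therapists.** Both arms receive usual care, and the word may refer to the clinicians who give it locally. Site stratification does balance the between-site part of that variation. This stands in part: the sentence draws no such distinction, and under either reading it does not cover the CBT therapists.

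**A clustering analysis is detail for a fuller document.** A reader might infer that the plan dropped a needed step. The article does not support that: it never mentions such a step, and an unadjusted chi-square does not preclude a second analysis. What remains is not silence. The article states a property that stratification lacks, and it names a test that assumes independence.

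**The size is assumed, and its upper end is demanding.** This stands. At ICC 0.10, therapists would have to differ by an SD of 15 points, nearly the full planned effect. If CBT changed nobody's outcome, CBT therapists would add no clustering and the error rate would stay at 5%. The manual, the experience and training of the therapists, two-weekly supervision and the fidelity ratings all aim to reduce therapist variation. A chi-square that ignores the site strata also tends to give slightly too wide a standard error, which may offset part of the effect.

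**No analysis separates a good therapist from a good therapy.** This also stands. It applies to any add-on psychotherapy trial, and the remedy should not be presented as curing it.

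**Conclusion.** The point holds in a limited form. Stratifying by site balances institution, region and the local usual-care setting; it neither balances nor removes differences between therapists who work in one arm only. The unadjusted chi-square can therefore have too small a standard error.

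The inflation could be negligible (5.2% at caseload 5 and ICC 0.01) or material (7.7% at caseload 10 and ICC 0.05). The 13% corner is an extreme case and not an expectation. All of this rests on assumed caseloads and ICCs and on a positive correlation within therapist.

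A reader might go further and conclude that the trial's intervals *are* too narrow, or that the comparison is biased. The article supports neither: it gives no figure from which the ICC could be judged, and the issue concerns precision and error rate while the randomised allocation is untouched.

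**What to change.** 1. In Randomisation, limit the rationale to institution and region, and local usual care if that was meant.
2. Record the treating CBT therapist for every patient in the CBT arm.
3. Keep the chi-square, and pre-specify beside it a comparison with site as a factor, therapist as a cluster in the CBT arm and each control patient as an own cluster. Either cluster-robust standard errors with a small-sample correction or a partially nested model with a therapist random effect in the CBT arm would serve.
4. Report the number of therapists, their caseloads, and the therapist ICC with its interval.

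Cost: one edited sentence, one data field and one extra analysis, with no change to sample size or conduct. The interval in that analysis may be somewhat wider, and the ICC will be imprecise if therapists are few. If therapist identity is not recorded during the trial, the question may not be answerable afterwards.

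### A single, openly stated block size of ten within each site makes up to one assignment in six predictable to staff who keep count of earlier allocations

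*Protocol article*

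**What the plan says.** All references are to the protocol article, Methods/Design.

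- **Randomisation.** Allocation is stratified by site, and "the randomisation will be performed separately for each research site, in random permuted blocks of ten". The stated purpose is "To guarantee a numeric balance across conditions". Lists come from a web-based system and are held remotely, an independent person allocates, and randomisation follows consent. The section adds: "The randomisation status is confirmed by fax to the randomisation bureau by the different sites". It mentions neither varying block sizes nor keeping the size from sites.
- **Intervention.** The experimental arm has up to 25 CBT sessions on top of usual treatment, so the arm is evident to patients and treating staff.
- **Design.** "The assessors are blinded to the research condition by not being able to check the patient status". Assessors also record a guess of the arm at each major assessment, as a check on blinding.
- **Power calculation.** The requirement is given per arm ("2 × 93 for the reduction of the transition to psychosis"), and "we decided to include 240 persons in the trial".
- **Analyses.** The group comparison is an unadjusted chi-square. Correction for risk factors follows only if baseline balance is found to be disturbed.

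**The concern.** Concealment has two parts. The list must be hidden, and the next assignment must not be inferable from those already made. The article secures the first. A constant block size leaves the second open: once five patients in a block have gone to one arm, all remaining places in that block belong to the other.

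The past allocations needed for this are available at the sites. Sites confirm randomisation status by fax, and CBT is visibly added to usual treatment.

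At stake is selective entry. Eligibility depends partly on interviewer-rated CAARMS and SOFAS scores, and consent precedes randomisation. Someone who could foresee the next arm could therefore influence who is approached, or when. If prognosis then differed between arms, the unadjusted comparison of transition rates would carry that difference.

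**Working it through.** The article gives no predictability figure, so there is none to reproduce.

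**Inputs**
- Block size 10 within site (Randomisation).
- Ratio 1:1, so 5 + 5 per block. The article does not state the ratio; it is inferred from the numeric-balance statement and the equal arms in the sample size.
- Planned total 240, equivalent to 24 blocks.
- Four sites: three screening regions ("referred to the mental health services in The Hague, Rivierduinen (Leiden and surroundings) and the province of Friesland") and the Amsterdam clinic (Participants). Sixty patients per site (240/4) is an assumption, used only in the simulation.

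**What an observer needs.** With a constant size, blocks begin at site patients 1, 11, 21 and so on, and each complete block adds exactly five CBT patients. If *n* patients have been randomised at the site and *c* of them to CBT, then:
- position in the current block = *n* mod 10;
- CBT places used in it = *c* − 5 × floor(*n*/10).

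Two running totals are enough; the order of allocations is not needed.

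**Determined assignments.** There are C(10,5) = 252 equally likely blocks. Position *k* is determined if one arm has been used up in the first *k* − 1 places.

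| Position | Blocks in which it is determined | Probability |
|---|---|---|
| 1 to 5 | 0 | 0% |
| 6 | 2 | 0.8% |
| 7 | 12 | 4.8% |
| 8 | 42 | 16.7% |
| 9 | 112 | 44.4% |
| 10 | 252 | 100% |

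The sum is 420/252 = 1.667 per block, which agrees with the closed form 2*m*/(*m* + 1) = 10/6 for *m* = 5. The share is 16.7%.

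**Over the trial.** If all blocks are complete, 24 × 1.667 = 40 of 240. Incomplete final blocks lower this. The least favourable split over four sites leaves 21 complete blocks and remainders such as 7, 7, 8 and 8: 21 × 1.667 + 2 × 0.056 + 2 × 0.222 = 35.6. The range is therefore about 36 to 40.

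**Correct guesses.** Always guessing the arm with more places left gives [*m* + 2^(2*m*−1)/C(2*m*,*m*) − 1/2]/(2*m*) = (5 + 512/252 − 0.5)/10 = 65.3%, against 50% by chance.

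**Other fixed sizes.** The determined share is 1/(*m* + 1): 33% for blocks of four, 25% for six, 16.7% for ten.

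**Varied sizes.** This was simulated with sequences of 60. The observer knows the set of possible sizes and every earlier allocation in order, but not where blocks end.

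| Scheme | Determined | At least 80% sure | Guessed correctly |
|---|---|---|---|
| Fixed 10 | 16.7% | about 19% | 65.3% |
| Random 8, 10, 12 | about 1.5% | about 11% | about 64.7% |

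1.5% of 240 is about 4 patients. Varying the size removes most of the certain assignments and some of the near-certain ones. It does little to the average guess.

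**The case against.** **The observer is hypothetical.** The figures need someone who keeps the site's totals, knows the block size and influences entry. The article does not say who sends the fax, whether recruiters see allocations, or whether sites were told the block size while recruiting. This stands, and is why 16.7% is an upper bound and not an estimate of what happens. It does not remove the weakness, because two running totals suffice and the article itself prints the size.

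**Safeguards exist.** The list is remote, the allocator independent, and consent comes first. These are sound, but none prevents prediction from past allocations, and consent before randomisation does not stop a consent discussion from being delayed.

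**Entry is systematic.** Three regions screen all referrals in the age range with a self-report questionnaire and a fixed cut-off, and CAARMS and SOFAS thresholds are specified. This narrows the room for selection without closing it, since those ratings and the timing of entry still involve judgement.

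**The analysis can adjust.** The Analyses section checks baseline balance, including symptom severity, and corrects if it is disturbed. That answers selection on measured severity. It cannot address selection on prognostic impressions that were not measured.

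**Ten is already a large block, and the average guess hardly changes.** Both are true. The gain is confined to the certain and near-certain assignments, which are the easiest to exploit.

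**A stronger reading to avoid.** A reader might infer that outcome assessors can deduce allocations, so that blinding of the primary endpoint fails. The article does not support this. Assessors are denied access to patient status, and their guesses are recorded. An assessor would first have to learn the arms of most other patients in a block, and nothing suggests that they do.

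**Conclusion.** The point holds as a design weakness that is cheap to remove, not as an error or contradiction. One stated block size of ten per site leaves up to one assignment in six (16.7%, about 36 to 40 of 240) predictable to site staff who count earlier allocations by arm and know the size.

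This rests on 1:1 allocation, which is inferred, and on an observer whom the article makes possible but does not show to exist. It would go too far to say that these assignments are in fact known before entry, or that selection has occurred. No claim is made about assessor blinding.

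**What to change.** Keep stratification by site and the web-based system, but let it draw block sizes at random, for example from 8, 10 and 12. Replace the sentence naming blocks of ten with one saying that sizes vary at random and are withheld from sites until recruitment ends. If recruitment has begun, apply this to all blocks not yet opened. Smaller sets are less attractive: 4, 6 and 8 would leave 2.1% determined and raise the guess rate to 67.8%.

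The cost is one system setting and one sentence, with no extra patients. The only statistical price is that the largest possible imbalance within a site rises from 5 (half of 10) to 6 (half of 12).
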